**Drug recovery**												
**Changes in drug use**			**√.**	**√.**	**√.**	**√.**	**√.**	**√.◎**	**√.◎**	**√.◎**	**√.◎**	**√.◎**
**Record complications**			**√.**	**√.**	**√.**	**√.**	**√.**	**√.◎**	**√.◎**	**√.◎**	**√.◎**	**√.◎**
**Combined medication**			**√.**	**√.**	**√.**	**√.**	**√.**	**√.◎**	**√.◎**	**√.◎**	**√.◎**	**√.◎**
**Adverse event**			**√.**	**√.**	**√.**	**√.**	**√.**	**√.◎**	**√.◎**	**√.◎**	**√.◎**	**√.◎**
**Causes of shedding**												

“√” means that it must be recorded; “√.” means that it should be recorded if it occurs; The part with this symbol “**◎**” means that you need to fill in if there is information; main symptoms and signs should be recorded until leaving the group; routine stools, stool culture, and safety indicators should be reviewed when leaving the group; efficacy determined on 5th day and patients who have not recovered should also be reviewed

### Outcome assessment

#### Primary outcome measures

Antibiotic use rate and clinical cure rate

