**Methods:**

This randomized, double-blind, placebo-controlled clinical trial has completed ChiCTR registration. The trial will randomly divide 120 children who meet the inclusion criteria into three groups: experimental group 1 (basic treatment + Gegen Qinlian decoction granules + Erbai drink placebo), experimental group 2 (basic treatment + Erbai drink granules + Gegen Qinlian decoction placebo), and control group (basic treatment + Gegen Qinlian decoction placebo + Erbai drink placebo). The main efficacy indicators will be antibiotic use rate and clinical cure rate, and the secondary efficacy indicators will be time to antibiotic intervention, effective rate, and course of treatment determined after 5 days. The following physical and chemical indicators will be measured: routine blood parameters, procalcitonin, C-reactive protein, electrocardiogram, liver and kidney function, electrolytes, routine urinalysis, routine stool analysis, and stool culture (including drug sensitivity).

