Erbai drink is an empirical prescription used by the master of traditional Chinese medicine, Wang Lie. This prescription is used to treat diarrhea of damp-heat type in children. However, in the existing guidelines [12], the prescription for pediatric damp-heat diarrhea is Gegen Qinlian Decoction, But, in clinical application, the master of Chinese medicine Wang Lie found that Erbai drink also has a significant effect in the treatment of diarrhea in children with damp-heat type. Wang et al. [13] summarize Wang Lie’s experience and found that Erbai drink is “harmonizing spleen yin and yang, clearing heat, promoting diuresis and detoxifying,” which is used to treat diarrhea in children with damp heat.

Erbai drink granules: Radix Paeoniae Alba (Bai Shao) 10 g, Rhizoma Atractylodis Macrocephalae (Bai Zhu)10 g, Radix scutellariae (Huang Qin) 10 g, Semen Coicis (Yi Yiren ) 10 g, Rhizoma Atractylodis (Cang Zhu) 5 g, Semen Plantaginis (Che Qianzi)10 g; Gegen Qinlian decoction granules: Radix Puerariae lobatae (Ge Gen) 10 g, Radix Scutellariae (Huang Qin) 10 g, Rhizoma Coptidis (Huang Lian) 5 g, Radix Glycyrrhizae (Gan Cao) 5 g. Two Chinese medicine prescriptions can all clear away heat, eliminate dampness ,and stop diarrhea for children with damp-heat diarrhea, but it can be found from the composition of the medicine that Gegen Qinlian decoction has a better heat-clearing effect and Erbai drink has a better dampness-eliminating effect. So, we hope that this difference can be verified in actual clinical observations.

Therefore, it is necessary to implement clinical trials to determine the safety and efficacy of TCM (Gegen Qinlian decoction and Erbai drink) in the treatment of antibiotic-resistant bacterial diarrhea in children.

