### Study design

This randomized, double-blind, placebo-controlled clinical trial will compare two different TCM preparations with a blank control group. The trial design is shown in Fig. 1.

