### Statistical analysis

Statistical analysis will be carried out using SAS 9.4 or above. According to the data characteristics, measured data will be analyzed by independent sample *t* tests or rank sum tests for comparison between groups and numerical data will be analyzed by χ^2^or Fisher’s exact probability tests. Laboratory data for all clinical endpoints will be analyzed according to intention to treat (ITT) and compliance (PP) analyses, and safety analysis will be performed using a safety data set (SS). The efficacy scores at the time of patient enrollment, intermediate follow-up (day 3, day 4 to day 7 after treatment), and at the end point of the trial will be calculated, and the mean, standard deviation, median, P5, P75, maximum and minimum values of the differences in values between baseline and the treatment period will be used. PP and ITT will be adopted to analyze the main index and overall index. Subjects with positive urine culture indicators will be included in the statistical subgroup to analyze the correlation between the study program and the overall efficacy evaluation index. Because this is a multicenter, randomized, double-blind controlled trial, the possible central effect on efficacy indicators should be considered.

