### Quality control

#### Sample size

We calculated the sample size according to our primary study. We found that the use rate of antibiotics in the two groups of patients treated with traditional Chinese medicine was 46% and that of the control group was 80%. Calculate the sample size under the settings of α = 0.05 and β = 0.80. The grouping ratio is 1:1:1. Calculate the single group n = 37, so there are 111 cases in the three groups. Taking into account a drop-out of 10%, In the end, we set the number of cases to 120.

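### Two primary endpoints and two arm-versus-control comparisons share one α of 0.05 with no stated success rule, and only antibiotic use is sized; if any win counts, the false-positive rate is about 16%

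*Protocol article*

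**What the plan says.** - **Endpoints.** The Primary outcome measures section reads, in full, "Antibiotic use rate and clinical cure rate". The Methods part of the abstract gives the same pair: "The main efficacy indicators will be antibiotic use rate and clinical cure rate". Neither place ranks the two or says whether one or both must succeed.
- **Comparisons.** Under Study design the trial "will compare two different TCM preparations with a blank control group", so there are at least two active-versus-control comparisons. The Background notes that the two preparations should differ in their effects and adds: "So, we hope that this difference can be verified in actual clinical observations".
- **Error rate and size.** The Sample size section says: "Calculate the sample size under the settings of α = 0.05 and β = 0.80". The value 0.80 can only be the power. The rates are given as "use rate of antibiotics in the two groups of patients treated with traditional Chinese medicine was 46% and that of the control group was 80" per cent, and the result is 37 per group, 111 in all, raised to 120 for 10% dropout. No cure rate is assumed anywhere.
- **Tests.** The Statistical analysis section lists t or "tests or rank sum tests for comparison between groups and numerical data will be analyzed by" χ² or Fisher. It mentions no testing order, adjustment or overall three-group test that comes first.

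**The concern.** Two endpoints times two active-versus-control comparisons make four primary tests, and the only α in the document is 0.05. Without a success rule, one P < 0.05 among the four could be reported as a positive trial. The article wants its results to support guidelines and a reduction in antibiotic use, so the error rate behind a positive claim matters. Clinical cure also carries primary status although no cure rate was assumed. The document therefore gives no basis for judging whether 37 per arm is enough for that endpoint.

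**Working it through.** **1. The plan's own figure.** Inputs from the Sample size section: p₁ = 0.46, p₂ = 0.80, mean 0.63, difference 0.34, α = 0.05 (taken as two-sided), power 0.80.

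Uncorrected: n = [1.960·√(2·0.63·0.37) + 0.842·√(0.46·0.54 + 0.80·0.20)]² / 0.34² = (1.338 + 0.538)² / 0.1156 = 30.4, so 31.

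With continuity correction: (n/4)·[1 + √(1 + 4/(n·0.34))]² at n = 30.45 gives 36.09, so **37**. This reproduces the stated figure: one pairwise comparison, one endpoint, unadjusted two-sided 0.05.

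**2. Family-wise error when nothing works.** Each test is at two-sided 0.05. Two comparisons that share a control arm have correlation 0.5. Four fully independent tests would give 1 − 0.95⁴ = 18.5%. Simulated z-tests (2,000,000 runs), with correlation ρ between the endpoints from 0 to 0.9, give:

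| Reading of the plan | Chance of at least one false positive |
|---|---|
| Antibiotic use only, two arms versus control | 9.1% |
| Either endpoint, either arm (4 tests) | 17.3% (ρ = 0), 16.1% (0.5), 12.6% (0.9) |
| As above plus preparation versus preparation (6 tests) | 22.9% (ρ = 0), 21.3% (0.5), 16.7% (0.9) |
| One three-group test per endpoint | 9.8% (ρ = 0) to 7.1% (0.9) |
| Both endpoints must win in the same arm | 0.5% (ρ = 0) to 5.5% (0.9) |

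Binomial check with uncorrected χ², 37 per arm, antibiotic use 80% in every arm, cure **assumed** 60% in every arm, latent correlation 0 to −0.8: about 5% for one test, 9% for antibiotic use in two arms, 16% to 17% for four tests, 21% to 22% for six, and about 0.4% to 1.2% if both endpoints must win in the same arm. The two methods agree.

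**3. Power for antibiotic use if two comparisons share 0.05.** At α = 0.025 each, 1.960 becomes 2.241. The uncorrected formula gives (1.530 + 0.538)² / 0.1156 = 37.004, so 38. The corrected formula gives 42.7, so 43. Exact power for 46% versus 80% at α = 0.025:

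| Per arm | Uncorrected χ² | Fisher |
|---|---|---|
| 37 | 80.5% | 73.4% |
| 36 (120 less 10% = 108, over 3) | 78.8% | 71.4% |

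**4. The alternative of splitting α over all four tests** (0.0125 each) needs 44 per arm uncorrected or 50 corrected, for antibiotic use alone. At 37 per arm, exact χ² power is about 72%. Power for cure cannot be computed, because no cure rates are given.

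**The case against.** Four points deserve weight.

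- **Missing analysis plan.** Adjustment methods and testing order often sit in a statistical analysis plan, and none is shown here. This stands: the most one can say is that no control is stated in this document. It does not cover everything. The two primary endpoints, the one α and the sizing on one endpoint are fixed here, and they do not fit together.
- **No single error rate follows from the text.** A reader might infer that the trial's false-positive rate simply is 16% to 17%. The document does not support that. The figure needs an any-win rule, exactly four tests at two-sided 0.05, and low to moderate correlation between endpoints. The χ² wording also allows one three-group test per endpoint, and a both-must-win rule would bring the rate to about 5% or below. Adjusting for two distinct treatments against a shared control is also not universal practice.
- **Comparison of the two preparations.** The Background expresses a hope and Study design names only comparisons with control. Counting this as a primary test, or faulting the sample size for giving it no planned effect, would overread the text. The six-test figures apply only if it is in fact tested.
- **Apparent allowance for two comparisons.** Since the uncorrected formula at α = 0.025 comes to 37.004, a reader might infer that 37 per arm was chosen to cover both arms. The article states 0.05, the corrected formula at 0.05 gives 37 exactly after rounding, and 37.004 would round up to 38. The match is a coincidence and shows no intended adjustment.

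**Conclusion.** The concern holds in conditional form. Two primary endpoints, two comparisons with control and one α of 0.05 stand together with no success rule, and the sample size covers antibiotic use only. Under an any-win rule with four two-sided 0.05 tests, the family-wise error is about 16%, with a range of 13% to 17% over endpoint correlations of 0.9 down to 0. The other readings run from under 1% to about 23%. That spread is itself the defect, because the rule that decides between these readings is not written down. The figures assume no effect of either preparation on either endpoint, and the binomial check further assumes 60% cure. The structure of the problem is certain; the size is known only as a range.

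**What to change.** State the success rule before the data are unblinded. One form that fits the existing sizing:

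1. Make antibiotic use rate, the only endpoint sized, the single primary endpoint.
2. Test each preparation against control with Holm at overall 0.05.
3. Test clinical cure only in an arm that wins on antibiotic use, under a named gatekeeping procedure that keeps the overall 0.05. Testing cure at a fresh 0.05 after Holm would spend the same α twice.
4. Report preparation versus preparation as an estimate with confidence interval only.
5. In the Sample size section, restate power at α = 0.025 per comparison and name the test, since χ² and Fisher differ by about 7 percentage points here.

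Other rules, such as requiring both endpoints or splitting α over four tests, would also remove the ambiguity. The split would need 44 to 50 evaluable per arm for antibiotic use alone, and either rule would need cure-rate assumptions.

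**Cost.** This is a change of wording, and no extra patients are proposed. Clinical cure loses co-primary status. Power at the stricter α is about 80% with uncorrected χ² at 37 per arm and 79% at 36. With Fisher it is 73% and 71%, so the article should not go on claiming 80% without naming the test.

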#### Secondary outcome measures

Time to antibiotic intervention, effectiveness, and treatment course.

### Safety outcomes

Abnormal liver and kidney functions, electrocardiogram, and other results; allergic symptoms such as drug fever, allergic reactions, anaphylactic shock, or skin rash; severe vomiting, diarrhea, and other digestive system symptoms; cough, chest tightness, shortness of breath, and other respiratory symptoms; and all adverse events that occurred in the trial.

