One course of treatment for the above three groups will last 5 days, and one to two courses can be administered continuously. The specific observation time and related items are shown in Table 1.

**Table 1 Tab1:** Specific observation time and related items

Stage		Enrollment	Clinical observation time (days)									
**Date of visit**		**0**	**1**	**2**	**3**	**4**	**5**	**6**	**7**	**8**	**9**	**10**
**Case screening**		**√**										
**Sign informed consent**		**√**										
**Random entry group**		**√**										
**Delivery of test drugs**		**√**										
**CRF completed**		**√**	**√**	**√**	**√**	**√**	**√**	**√◎**	**√◎**	**√◎**	**√◎**	**√◎**
**Basic medical history**		**√**										
**General information**		**√**										
**General inspection items**	**Physical examination**	**√**	**√**	**√**	**√**		**√**	**√◎**	**√◎**	**√◎**	**√◎**	**√◎**
	**Routine blood test**	**√**	**◎**	**◎**	**√**	**◎**	**◎**	**√◎**	**√◎**	**√◎**	**√◎**	**√◎**
	**Procalcitonin**	**√**	**◎**	**◎**	**√**	**◎**	**√**	**◎**	**◎**	**◎**	**◎**	**◎**
	**C-reactive protein**	**√**	**◎**	**◎**		**◎**	**◎**	**√◎**	**√◎**	**√◎**	**√◎**	**√◎**
	**Electrocardiogram**	**√**					**√**	**√◎**	**√◎**	**√◎**	**√◎**	**√◎**
	**Liver and kidney function**	**√**					**√**	**√◎**	**√◎**	**√◎**	**√◎**	**√◎**
	**Electrolytes**	**√**					**√**					
	**Routine urine test**	**√**					**√**					
	**Routine stools**	**√**	**◎**	**◎**	**√**	**◎**	**√**	**√◎**	**√◎**	**√◎**	**√◎**	**√◎**
	**Stool culture (including drug sensitivity)**	**√**					**√**	**√◎**	**√◎**	**√◎**	**√◎**	**√◎**
**Stool characteristics**		**√**	**√**	**√**	**√**	**√**	**√**	**√◎**	**√◎**	**√◎**	**√◎**	**√◎**
**Stool frequency**		**√**	**√**	**√**	**√**	**√**	**√**	**√◎**	**√◎**	**√◎**	**√◎**	**√◎**
**Symptom evaluation**		**√**	**√**	**√**	**√**	**√**	**√**	**√◎**	**√◎**	**√◎**	**√◎**	**√◎**
**Temperature card**		**√**	**√**	**√**	**√**	**√**	**√**	**√◎**	**√◎**	**√◎**	**√◎**	**√◎**

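### Safety outcomes are counted over each child's own time in the trial, which appears to run from 5 to 10 days depending on recovery, so simple proportions would mix harm with length of observation if recovery differs by arm

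*Protocol article*

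**What the plan says.** All references are to the protocol article.

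- **What is counted.** Safety outcomes lists "Abnormal liver and kidney functions, electrocardiogram, and other results", several groups of symptoms, "and all adverse events that occurred in the trial". No time window is attached.
- **How long a child is treated.** The text above Table 1 says: "One course of treatment for the above three groups will last 5 days, and one to two courses can be administered continuously".
- **How long a child is observed.** The footnote to Table 1 says that "main symptoms and signs should be recorded until leaving the group" and that "routine stools, stool culture, and safety indicators should be reviewed when leaving the group". It adds: "efficacy determined on 5th day and patients who have not recovered should also be reviewed".
- **What Table 1 requires.** Adverse events are entered if they occur, on days 1-5 and conditionally on days 6-10. ECG and liver and kidney function carry an unconditional mark on days 0 and 5. On days 6-10 they carry a combined mark, one part of which "means that you need to fill in if there is information".
- **How it is analysed.** Statistical analysis assigns safety to a safety data set. Its only methods for counts are chi-square and Fisher's exact tests, given in a general sentence. No adjustment for length of observation is mentioned.
- **What is recorded.** Adverse events asks for the time and duration of each reaction.

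**The concern.** Read together, these sections make the safety counting period each child's own stay in the trial. The length of that stay appears to depend on recovery at day 5. Recovery is a post-randomisation result that the treatments are meant to change: clinical cure rate is a primary outcome and treatment course a secondary one.

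A child observed for 10 days has more opportunity to have an adverse event than a child observed for 5. A child tested on day 5 and again at exit has two chances of an abnormal result instead of one. If the share of children continuing differs by arm, a comparison of simple proportions attributes part of that difference to the products. Randomisation and blinding do not remove this, because the imbalance arises after allocation and through efficacy.

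Monitoring adverse events and laboratory parameters is a stated study aim. With 40 children per arm (120 / 3), readers will judge safety mainly from the observed proportions.

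**Working it through.** The article has no safety figure to reproduce. It gives no recovery rates, adverse-event rates or abnormal-test rates, so every rate below is an assumption. Only the day counts and the test schedule come from the document.

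**Inputs**
- Observation: 5 days for a child who leaves after one course, 10 days after two (text above Table 1; exit at day 5 is inferred).
- Post-baseline ECG and liver/kidney tests: one (day 5) for a child who leaves then; two (day 5 and exit) for a child who continues (Table 1 and footnote).
- Assumed: c = share continuing past day 5; h = daily risk of an adverse event, the same in all arms; 5% chance of an abnormal result per test.

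**Mean observation time** = 5 + 5c. At c = 0.6 this is 8.0 days; at c = 0.3 it is 6.5 days.

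**Share with at least one adverse event** = c(1 − e^(−10h)) + (1 − c)(1 − e^(−5h)).

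At h = 0.04, 1 − e^(−0.4) = 0.3297 and 1 − e^(−0.2) = 0.1813.
- c = 0.6: 0.6 × 0.3297 + 0.4 × 0.1813 = 0.270
- c = 0.3: 0.3 × 0.3297 + 0.7 × 0.1813 = 0.226

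| Daily risk h | 60% continuing | 30% continuing | Apparent ratio |
|---|---|---|---|
| 0.02 | 14.7% | 12.1% | 0.82 |
| 0.04 | 27.0% | 22.6% | 0.84 |
| 0.08 | 46.2% | 39.6% | 0.86 |

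The true ratio is 1 in each row. At h = 0.04, with 30% continuing in the faster arm, the ratio is 0.94 if 40% continue in the slower arm and 0.79 if 70% do. It is 1.00 if the shares are equal. If the shares are swapped between arms, the ratio inverts.

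**Share with any abnormal test** = c(1 − 0.95²) + (1 − c) × 0.05, with 1 − 0.95² = 0.0975.
- c = 0.6: 0.0585 + 0.0200 = 7.85%
- c = 0.3: 0.02925 + 0.0350 = 6.43%
- Ratio 6.43 / 7.85 = 0.82

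**In children, at 40 per arm.** Adverse events (h = 0.04): 40 × (0.270 − 0.226) = about 1.8. Abnormal tests: 40 × (0.0785 − 0.0643) = about 0.6.

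**Chance of a significant test from this alone.** For 60% versus 30% continuing and daily risks of 1% to 5%, it is about 4% to 7% with 40 per arm, close to the nominal 5%.

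**Masking.** With 60% continuing in the slower arm and 30% in the faster, the two proportions are equal when the faster arm's daily risk is about 24% higher. At h = 0.04 in the slower arm, solving 1 − 0.3x² − 0.7x = 0.2703 gives x = 0.781, so h = −ln(0.781)/5 = 0.0494, and 0.0494 / 0.04 = 1.24.

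**Same assumptions under the proposed summaries**
- Days 1-5 only: 1 − e^(−0.2) = 18.1% in every arm, ratio 1.00 for any c.
- Events per child-day: 40 × 8.0 × 0.04 = 12.8 events in 320 child-days, and 40 × 6.5 × 0.04 = 10.4 in 260. Both are 0.04 per child-day.

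**The case against.** **This is analysis-plan content.** Time windows and exposure adjustment are normally set in the SAP, which is not shown, and collecting all adverse events is ordinary practice. No sentence commits to a single proportion with any event. This stands in part: an unseen plan may already deal with it, and the recorded event times leave the analysis open. But the point does not rest on a missing detail alone. The article itself defines the outcome over the whole stay, makes that stay variable, and names only tests of proportions.

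**Exit at day 5 is not stated.** This stands. No sentence says that recovered children leave then or names who takes a second course. The inference rests on the one-or-two-course rule, recording until exit, and the conditional marks on days 6-10.

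**The direction is unknown.** This stands. A reader might infer that the control arm will show more harm and the TCM arms will look safer. The article does not support that. It gives no recovery rates, and Test drugs allows ceftriaxone when a child worsens or fails to improve, so heavier antibiotic use in the control arm could narrow or reverse a gap in day-5 recovery. The 46% and 80% under Sample size are antibiotic-use rates and cannot stand in for non-recovery.

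**The effect is small.** This stands for hypothesis testing: a false significant result is hardly more likely than usual. The harm is a distorted estimate.

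**Tests on every day from 6 to 10.** Reading the combined marks as daily required tests would give six post-baseline tests and a ratio of 0.64 (11.4% versus 17.9%). That is an unlikely reading of a conditional mark, and no weight is placed on it.

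**Cutting the comparison at day 5 loses information.** This stands. Days 6-10 carry the longest study-drug exposure, so a day 1-5 comparison should not replace the full count.

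**Conclusion.** The point holds in a limited form. As written, the safety comparison covers a period that appears to depend on recovery, and the named tests do not allow for it. If recovery differs by arm, the arm with slower recovery shows more events and more abnormal tests at equal daily risk. If recovery is equal, there is no bias.

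The size rests wholly on assumed rates. With 60% versus 30% continuing, the apparent ratio is about 0.82 to 0.86 for adverse events and about 0.82 for tests (two post-baseline tests against one), or roughly one to two children per arm. It also rests on the inference that recovered children leave at day 5. The documents do not establish which arm would be favoured, nor that a misleading significant test is likely.

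**What to change.** Keep the full listing and count of all adverse events by arm. State in Statistical analysis that the between-arm safety comparison also includes:

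1. adverse events on days 1-5, and the day-5 ECG and liver and kidney tests, which Table 1 requires in every child;
2. all adverse events per child-day, with day 6-10 events and test results shown by arm, using child-days and the number of children tested as denominators.

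The two additions complement each other. The first is free of the recovery effect but omits the longest exposure. The second uses all the data but assumes a roughly constant daily risk. The day 6-10 figures describe children selected by non-recovery and should be read descriptively. It would also help to state when a recovered child's safety observation ends, since the article leaves this to inference.

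No extra visit, test or data item is needed, because event times and day-5 tests are already collected. The cost is one or two extra safety tables.
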